## Abstract

**Introduction:**

Inflammation plays a critical role in the pathogenesis of atherosclerosis, the leading cause of ischaemic heart disease (IHD). Studies in preclinical models have demonstrated that an increase in regulatory T cells (Tregs), which have a potent immune modulatory action, led to a regression of atherosclerosis. The Low-dose InterLeukin 2 (IL-2) in patients with stable ischaemic heart disease and Acute Coronary Syndromes (LILACS) study, established the safety of low-dose IL-2 and its biological efficacy in IHD. The IVORY trial is designed to assess the effects of low-dose IL-2 on vascular inflammation in patients with acute coronary syndromes (ACS).

**Methods and analysis:**

In this study, we hypothesise that low-dose IL-2 will reduce vascular inflammation in patients presenting with ACS. This is a double-blind, randomised, placebo-controlled, phase II clinical trial. Patients will be recruited across two centres, a district general hospital and a tertiary cardiac centre in Cambridge, UK. Sixty patients with ACS (unstable angina, non-ST elevation myocardial infarction or ST elevation myocardial infarction) with high-sensitivity C reactive protein (hsCRP) levels >2 mg/L will be randomised to receive either 1.5×10^6^ IU of low-dose IL-2 or placebo (1:1). Dosing will commence within 14 days of admission. Dosing will comprise of an induction and a maintenance phase. 2-Deoxy-2-[fluorine-18] fluoro-D-glucose (^18^F-FDG) positron emission tomography/CT (PET/CT) scans will be performed before and after dosing. The primary endpoint is the change in mean maximum target to background ratios (TBR_max_) in the index vessel between baseline and follow-up scans. Changes in circulating T-cell subsets will be measured as secondary endpoints of the study. The safety and tolerability of extended dosing with low-dose IL-2 in patients with ACS will be evaluated throughout the study.

**Ethics and dissemination:**

The Health Research Authority and Health and Care Research Wales, UK (19/YH/0171), approved the study. Written informed consent is required to participate in the trial. The results will be reported through peer-reviewed journals and conference presentations.

**Trial registration number:**

NCT04241601.

Strengths and limitations of this studyThis study explores the clinical efficacy of low-dose interleukin 2 (IL-2) in reducing vascular inflammation in patients acutely presenting with acute coronary syndrome (ACS), using a well-validated imaging biomarker (^18^F-FDG (2-deoxy-2-[fluorine-18] fluoro-D-glucose)).Changes that occur in a wide range of circulating lymphocyte subsets with extended dosing with low-dose IL-2 will be studied in the acutely presenting ACS patient population at multiple timepoints.The safety of extended dosing with low-dose IL-2 in patients acutely presenting with ACS will be studied in this trial, using multiple sources.Due to the early phase nature of this study, it is not powered to determine if treatment with low-dose IL-2 would lead to improvements in clinical outcomes.

## Introduction

### Atherosclerosis and inflammation

Inflammation plays a pivotal role in the initiation and progression of atherosclerosis, which accounts for an overwhelming majority of cardiovascular events. The role of the immune system in the pathophysiology of atherosclerosis and plaque instability is multifaceted and orchestrated by both the innate and adaptive components of the immune system.^1^ The Canakinumab ANti-inflammatory Thrombosis Outcomes Study reported for the first time that anti-inflammatory therapy significantly reduced recurrent cardiovascular events in patients with ischaemic heart disease (IHD) and ongoing inflammation with persistently raised high-sensitivity C reactive protein (hsCRP) levels.^2^ Further efforts to harness the immune system for pharmacological therapeutic strategies in cardiovascular disease are currently underway.^3 4^

Due to their critical role in mediating immune tolerance and antiatherosclerotic effects, natural and inducible regulatory T cells (Tregs) (CD4^+^CD25^+^FOPX3) are a focus of novel therapeutic strategies. Initial studies in preclinical models showed that Tregs reduced plaque inflammation, slowed progression and even led to the regression of atherosclerosis.^5 6^ Tregs have also been implicated in moderating the postischaemic immune responses triggered by self-antigens presented by necrotic myocardium.^7^ In line with this finding, it has also been demonstrated that Tregs promote myocardial wound healing, attenuate adverse left ventricular remodelling and improve cardiac function.^8–11^ The Malmo Diet and Cancer study further demonstrated an increased risk of acute coronary events in patients with low levels of baseline circulating Treg cells.^12^ Observational studies have also shown that patients with acute coronary syndrome (ACS) have lower numbers of circulating Tregs with impaired function.^13–16^ Furthermore, low levels of Tregs maybe also associated with plaque instability.^15^

Interleukin 2 (IL-2) plays a crucial role in immune homeostasis by determining the balance between T effector (Teffs) and Tregs.^17 18^ While IL-2 is implicated in the development of both Teffs and Tregs, unlike Teffs, Treg cells constitutively express an IL-2 receptor (IL-2Rα) which binds to IL-2 with high affinity, making this subset very sensitive to IL-2.^19^ Of the cytokines involved in Treg development and stability, IL-2 is the most essential.^20^

The administration of low-dose IL-2 has been used in autoimmune conditions such as graft versus host disease, autoimmune vasculitis, hepatitis, type 1 diabetes mellitus and systemic lupus erythematosus, to boost Treg numbers with promising results.^17 21–24^ Furthermore, a recent study involving patients with 11 autoimmune conditions demonstrated the clinical efficacy and safety of low-dose IL-2.^25^

## LILACS

The Low-dose InterLeukin 2 in patients with stable ischaemic heart disease and Acute Coronary Syndromes (LILACS) was the first study to explore the safety of low dose of IL-2 and its ability to expand Treg cells in this patient cohort. This was a double-blinded, randomised controlled adaptive phase I/IIa trial.^26^ Twenty-five patients with stable IHD were dosed in part A with aldesleukin (recombinant IL-2). The dose range used in this trial was between 0.3×10^6^ and 3×10^6^ IU. The ratio of IL-2 to placebo was 3:2 for each group. An increase in Treg cells was observed at the doses tested without any significant increases in Teff cells.^26^ Part B, which included patients with ACS (non-ST elevation myocardial infarction (NSTEMI) and unstable angina (UA)), was carried out on completion of part A. Two doses (1.5×10^6^ and 2.5×10^6^ IU) were used in part B (IL-2: placebo=6:2). In both parts, the low-dose IL-2 and placebo were administered for 5 consecutive days. Low-dose IL-2 was well tolerated in both patients with stable IHD and ACS. The most commonly occurring adverse reactions were injection site reactions, which were temporary. Other adverse reactions included influenza-like symptoms and myalgia. No serious adverse events (SAEs) were observed in part A. Two SAEs were noted in part B that were deemed to be unrelated to the investigational medical product (IMP). In LILACS, the target dose needed to achieve a 75% increase in Tregs was determined as 1.46×10^6^ IU.

Based on the promising results of LILACS, we hypothesised that low-dose IL-2 would reduce vascular inflammation in patients with ACS as assessed by 2-deoxy-2-[fluorine-18] fluoro-D-glucose (^18^F-FDG) positron emission tomography (PET)/CT imaging before and after treatment.

^18^F-FDG is the most widely used radionuclide in imaging inflammation in the context of atherosclerosis. Limitations of ^18^F-FDG include the fact that it cannot be used to quantify inflammation in coronary arteries reliably and that the ^18^F-FDG signal is not inflammatory cell specific as all glucose-metabolising cells take up ^18^F-FDG.^27–29^ However, with respect to atherosclerosis, ex vivo histological studies from arterial specimens have shown a strong correlation between ^18^F-FDG uptake and macrophage density.^30 31^ This is thought to be due to the increased glucose turnover in macrophages compared with other cells within the atherosclerotic plaque. Furthermore, ^18^F-FDG quantification is highly reliable and reproducible in large- to medium-sized vessels.^32^
^18^F-FDG PET/CT has been used by our group and others as a biomarker for drug development in phase II cardiovascular drug intervention studies.^33–35^
^18^F-FDG PET/CT has specifically been used to study the effect of statins and anti-inflammatory compounds on vascular inflammation.^36–40^

## Methods and analysis

The IVORY trial is a prospective, randomised, double-blind, placebo-controlled, phase II clinical trial. This is an academic study involving two centres namely, Cambridge University Hospitals (CUH) and Royal Papworth Hospital in Cambridge, UK. Overall study coordination, monitoring and auditing will be undertaken by the Cardiovascular Trials Office of the Cambridge Clinical Trials Unit (CCTU), CUH. The study is sponsored by CUH.

### Study population

To be included, participants must be admitted with a diagnosis of ACS. The study will include patients presenting with ST elevation myocardial infarction (STEMI), NSTEMI or UA. The participants should have symptoms suggestive of myocardial ischaemia lasting 10 min or longer at rest or on minimal effort and either have elevated levels of troponin on admission and/or dynamic ECG changes suggestive of ischaemia. Furthermore, to be included participants will require hsCRP levels >2 mg/L at screening. We hypothesise patients presenting with hsCRP levels >2 mg/L have residual systemic inflammation and are at higher risk of recurrent cardiovascular events. Therefore, recruitment will be restricted to these patients as they are most likely to benefit from this treatment.

Due to the ionising radiation associated with ^18^F-FDG PET/CT scans, to be included in the trial, women must be either postmenopausal, have had a documented hysterectomy and/or bilateral oophorectomy or sterilisation procedure or be perimenopausal with a negative pregnancy test at screening. Perimenopausal women will also have to comply with the use of contraception for the duration of the trial and undergo additional pregnancy tests during and after treatment.

Exclusion criteria include patients who present with cardiogenic shock, cardiac arrest and uncontrolled hypertension/hypotension. Blood tests will be carried out to exclude patients with thyroid, severe renal and hepatic dysfunction as specified in the protocol. Patients with active infection, history of malignancy requiring active treatment or on oral/intravenous immune suppression therapy will also be excluded. Patients with type 1, or type 2 diabetes mellitus with poor control, will be excluded due to the challenges in analysing ^18^F-FDG PET/CT scans in this patient cohort.^40^ Due to the ongoing pandemic and to minimise potential risk, patients who are COVID-19 positive on PCR at the time of screening will not be recruited to the trial. Detailed inclusion and exclusion criteria are listed in online supplemental table 1.

10.1136/bmjopen-2022-062602.supp2Supplementary data

We plan to recruit 60 patients for the IVORY study. The sample size is based on an absolute difference of 0.2 in the primary endpoint (mean maximum target to background ratio (TBR_max_) in the index vessel) between placebo and active treatment at the end of the dosing period. This is equivalent to a 10% difference from a reference value of 2.02 and equivalent to the size effect observed after atheroprotective therapy.^35–37^ This is based on the results of previous studies that have reported less than a 10% difference in mean TBR_max_ in the index vessel between active treatment and placebo and failed to reduce cardiovascular outcomes.^34 39 41–43^

Assuming an SD of 0.24, 24 patients per arm, testing at two-sided 5% significance level, would provide 80% power. Therefore, a sample size of 30 completed patients per arm was selected to account for participant dropout and poor-quality scans deemed to be unsuitable for analysis (eg, because of motion artefact). This sample size of n=30 per group also allows the detection of a baseline-corrected 6% difference in TBRmax in the index vessel for the trial primary endpoint (mean 0.125, SD 0.166) between placebo and active treatment at the end of the treatment period, at 2-sided 5% significance level and 80% power.

The study opened on 26 August 2020. Thirty-three participants have completed the trial to date, and we expect recruitment to be completed by December 2023, after which the data analysis will commence.

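### Thirty per arm serves both as the number entering and as the number completed, so the secondary claim of 80% power for a 6% difference holds only if almost nobody is lost

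*Protocol article*

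**What the plan says.** All of the sample-size text is in the Protocol article under Study population.

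- **Recruitment:** "We plan to recruit 60 patients for the IVORY study". The abstract (Methods and analysis) randomises the sixty 1:1, so 30 per arm enter.
- **Main basis:** "The sample size is based on an absolute difference of 0.2 in the primary endpoint", about 10% of a reference value of 2.02. "Assuming an SD of 0.24, 24 patients per arm, testing at two-sided 5% significance level, would provide 80% power".
- **Allowance for losses:** "a sample size of 30 completed patients per arm was selected to account for participant dropout and poor-quality scans".
- **Second claim:** "This sample size of n=30 per group also allows the detection of a baseline-corrected 6% difference in TBRmax in the index vessel". The text gives a mean of 0.125 and SD of 0.166, two-sided 5% significance and 80% power.

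Two other sections bear on the point. Under Lymphocyte subset and biomarker analysis, the full analysis population is limited to dosed patients who finished the treatment course. Under Image analysis, change from baseline is analysed by ANCOVA with baseline value and ST-elevation status as covariates.

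**The concern.** Going from 24 to 30 to cover dropout and unusable scans makes 30 the number before losses. Calling the 30 completed makes it the number after dropout. With 60 patients recruited, both can be true only if nobody drops out, and then no allowance would be needed.

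The second power claim uses the full 30, which spends the allowance the preceding sentence has just set aside. Losses do reduce the analysed number: non-completers fall outside the full analysis population, and the endpoint needs a usable scan at baseline and at follow-up.

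What is at stake is one stated power figure. The claim is worded for the primary endpoint on a baseline-corrected scale, so a reader may use it to judge how sensitive the trial was to a difference of about 6%. That sensitivity is lower than stated once a few patients per arm are lost.

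**Working it through.** **Inputs** (Study population): difference 0.2, SD 0.24, 24 per arm; difference 0.125, SD 0.166, 30 per arm; reference value 2.02; two-sided 5%; target power 80%.

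**Method.** Two-sample t test with equal arms of size n. The noncentrality is δ = (difference / SD) × √(n/2) with 2n − 2 degrees of freedom, and power is the probability that |t| exceeds its two-sided 5% critical value.

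**Step 1: reproduce the main calculation.** 0.2/0.24 = 0.833. At n = 24, δ = 0.833 × √12 = 2.887 and power is 80.7%. The required n is 23.6, so 24. The stated figure reproduces.

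**Step 2: reproduce the second claim.** 0.125/0.166 = 0.753. At n = 30, δ = 0.753 × √15 = 2.916 and power is 81.8%. The required n is 28.7, so 29. The claim is right if all 30 per arm are evaluable.

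**Step 3: the allowance.** 24/30 = 0.80, so the step from 24 to 30 covers a loss of up to 20%. The article states no loss rate; this is only what the two numbers imply.

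**Step 4: the second claim at smaller evaluable numbers** (0.125, SD 0.166):

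| Evaluable per arm | Power |
|---|---|
| 30 | 81.8% |
| 29 | 80.5% |
| 28 | 79.0% |
| 27 | 77.5% |
| 24 | 72.4% |

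The normal approximation gives 74.2% at 24. The t-test figures are used here because the t test also gives the plan's 24 per arm; the normal approximation gives 23.

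**Step 5: difference detectable with 80% power** (SD 0.166): 0.122 at 30 per arm (0.122/2.02 = 6.0%) and 0.137 at 24 per arm (0.137/2.02 = 6.8%).

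**Step 6: sensitivity to the planned ANCOVA.** The article does not say whether 0.166 is the SD of a change score or a covariate-adjusted residual SD. Assume that it is a change-score SD and that 0.24 is the SD at each visit.

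- Change-score variance: 0.166² = 2 × 0.24² × (1 − ρ), so 1 − ρ = 0.02756/0.1152 = 0.239 and ρ = 0.76.
- ANCOVA residual SD: 0.24 × √(1 − 0.76²) ≈ 0.156.
- Power for 0.125 is then about 78% at 24 per arm and about 81% at 26.

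If 0.166 is already a residual SD, the table in step 4 applies essentially as it stands.

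**The case against.** **The design power is intact.** The sample size is based on 0.2, and that calculation holds at 24 per arm (80.7%). The 6% sentence is a supplementary remark. This stands. A reader might infer that the trial as a whole is underpowered or must enrol more; the document does not support that.

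**72% is the low end, not a forecast.** A reader might take 24 evaluable per arm as the expected number. No loss rate is given, and 24 is the minimum the main calculation needs. This stands too: between no loss and the full allowance, the t-test power runs from 81.8% to 72.4%.

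**The planned analysis may be more efficient.** Under the assumption in step 6 the shortfall at 24 per arm is about 2 points. The article does not settle which SD is meant, so this tempers the figure without removing the point.

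**The 30 may be meant literally, with losses replaced.** The 6% claim would then stand. But the article mentions no replacement, and with any dropout, 30 completed per arm would need more than the 60 it recruits and randomises. Completing the course would also not guarantee a usable scan, which the same sentence lists as a separate loss.

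**The 10% benchmark.** The text supports its 10% target with earlier studies that found smaller differences between "active treatment and placebo and failed to reduce cardiovascular outcomes". A reader might infer that claiming sensitivity to 6% contradicts this, or that the result must be judged against 0.2. Neither follows. Saying that a sample can detect 6% does not make 6% the success criterion, a smallest significant difference below the design target is no defect, and Image analysis already commits to point estimates with 95% CIs.

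**Conclusion.** The point holds, limited to the wording of the number per arm and to the secondary 6% claim. Thirty per arm is used both as the number entering and as the number completed, which is inconsistent with recruiting 60 while allowing for losses. By a two-sample t test, the claim of 80% power for 0.125 (SD 0.166) needs at least 29 evaluable per arm and fails once two or more per arm are lost. At the full allowance of 24 evaluable it is about 72%, or equivalently 80% power for 0.137 (6.8%).

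These figures take 0.166 as the SD that applies in the analysis. Power at 24 per arm would be about 78% if 0.166 is a change-score SD and 0.24 the SD at each visit. The loss of up to 20% is inferred from 24 against 30 and is not a stated rate.

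**What to change.** Enrol no more patients. Amend the sample-size paragraph as follows:

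- State that 30 per arm are randomised and that at least 24 evaluable per arm are needed for the 0.2 target. Remove the description of the 30 as completed.
- Restate the 6% claim at the evaluable number: about 72% power at 24 per arm, or 80% power for a 6.8% difference. Alternatively, keep the claim and say explicitly that it needs at least 29 evaluable per arm.
- Say whether 0.166 is a change-score SD or a covariate-adjusted residual SD. If the restated power is calculated for the ANCOVA instead, give the SD and correlation assumed.

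The cost is a few words and a slightly less favourable secondary figure. Recruitment, the primary analysis and the main power calculation do not change.

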### Dose selection for IVORY

A dose of 1.5×10^6^ IU was selected for the study based on the analysis of data from the LILACS trial. In patients with ACS dosed in Part B of the LILACS trial, a dose of 1.5×10^6^ IU led to an 80% increase in Tregs after 5 consecutive days of treatment. No significant increases in Teff cells were noted at this dose.

#### Active drug description

Aldesleukin is produced by recombinant DNA technology using an *Escherichia coli* strain that contains a genetically engineered modification of the human IL-2 gene.

Commercially available aldesleukin with an UK marketing authorisation will be used and initially prepared as per the manufacturer’s guidance. This preparation will be diluted further using 5% glucose, to give a final concentration of 3.3×10^6^ IU/mL. The administration of aldesleukin will be by subcutaneous injection.

#### Placebo description

Commercially available dextrose 5% with an UK marketing authorisation at equivalent dose volume will be used for the placebo formulation.

### Study protocol

The trial will be performed in accordance with the spirit and the letter of the Declaration of Helsinki, the conditions and principles of Good Clinical Practice, the protocol and applicable local regulatory requirements and law. Participants will be provided with an information sheet and given the opportunity to consider the information for at least 24 hours. They will have an opportunity during this time to discuss the study with trial staff and have any queries answered before consenting to participate in the trial. Full informed consent (online supplemental file) will be taken at the screening visit (V1) by the study team. The screening visit will also include baseline blood tests, a physical examination, vitals (blood pressure, heart rate, temperature), a clinical history and ECGs in triplicate. The screening bloods will include safety blood tests (full blood count, electrolytes/urea/creatinine, liver function tests), thyroid function tests, hsCRP, serum/urine pregnancy test where applicable and a full lipid profile.

10.1136/bmjopen-2022-062602.supp1Supplementary data

Each participant who passes screening will be assigned an ID number. The research team will complete a case record form (CRF) for each encounter with the participant. Data are then sent to the CCTU for entry into the electronic trial database. All CRFs will be stored safely, and patient identifiable information is kept confidential.

Randomisation will then be carried out using sealed envelope (www.sealedenvelope.com). Randomisation will be stratified by ST elevation status to minimise bias between the groups since patients with STEMI typically have higher circulating hsCRP levels.

During the trial, the patient facing trial team, patients and data analysis teams (immunology sample analysers and image analysers) are blinded to the treatment allocation. To maintain the overall quality and legitimacy of the clinical trial, unblinding will only occur in exceptional circumstances when knowledge of the actual treatment is essential for further clinical management of the patient.

The trial design is summarised in figure 1. After randomisation, patients will undergo an ^18^F-FDG PET/CT scan covering the ascending aorta and carotid arteries (V2).

**Figure 1 F1:**
[figure not shown]
Summary of trial design. ^18^F-FDG, 2-deoxy-2-[fluorine-18] fluoro-D-glucose; NSTEMI, non-ST elevation myocardial infarction; PET, positron emission tomography; STEMI, ST elevation myocardial infarction.

The ^18^F-FDG PET/CT scans will be carried out in CUH. Patients would be instructed to fast for 6 hours prior to scanning. A finger prick blood sugar test will be performed prior to the PET/CT scan. A carotid angiogram will be undertaken after the PET/CT scan where possible. The carotid angiogram can be performed either in visit 2 or 15, as this is for anatomical correlation to enable more accurate measurement of ^18^F-FDG uptake in the carotid arteries. A transthoracic echocardiogram will also be undertaken prior to dosing to assess the left ventricular function and regional wall motion abnormalities.

Dosing will commence within 14 days of admission, and after the baseline ^18^F-FDG PET/CT scan (figure 2). Dosing will consist of two phases spanning a period of 8 weeks. The induction phase will involve once daily subcutaneous injections of IMP for 5 days (V3–V7). During the maintenance phase, participants will receive once weekly subcutaneous injections of IMP for 7 weeks. Dosing visits will last up to 1 hour during the induction phase. At each visit, participants will be screened for potential side effects and their medications will be reviewed by a clinician. Participants will also undergo a physical examination, have their vital signs measured, have ECGs recorded and safety bloods taken. Circulating systemic inflammatory biomarkers (hsCRP, interleukin 6), cardiac troponin I and lymphocyte subsets will be measured on V3 and V7.

